### Measurement

The MATE [13] is a semi-structured interview that is based on the World Health Organisation’s biopsychosocial model of health [22]. It includes 10 modules assessing alcohol and drug use during the past 30 days and the person’s lifetime, substance abuse treatment history, psychiatric and physical co-morbidity and symptom severity, diagnosis of substance -use disorder and its consequences for the person’s everyday life, need for care, and social stability. The MATE yields 20 sum scores, which again can be summarized into four dichotomized so called dimension scores: Addiction severity, severity of psychiatric co-morbidity, severity of social disintegration, and history of treatment for a substance-use disorder. With the use of these four dimensions, a recommendation for referral to one of four LOCs can be made [13]. A computer-assisted version of the MATE is available; administering it takes approximately 45 minutes to complete. The MATE-scores, including the recommendation of one of the four LOCs (LOC 1: Outpatient advice; LOC 2: Outpatient treatment; LOC 3: Day/Residential treatment; LOC 4: Care), are calculated automatically. The MATE has been shown to have acceptable psychometric properties, and it was found to be feasible for use in routine care and in research settings in both the Netherlands and Germany [14,23].

The MATE-Outcomes is an abbreviated version of the MATE, which was developed as a follow-up assessment for treatment evaluation purposes.

The Client Sociodemographic and Service Receipt Inventory (CSSRI-EU) is a standardized Europe-wide validated instrument to evaluate health-service utilization and medication use for the domain of mental-health care [24]. Using the data on health service utilization, health care costs can be estimated in a second step via monetary valuation with unit costs. The CSSRI-EU can be conducted as an interview; it takes approximately 20 minutes to complete. The validity of the German version of the instrument [25] and cost implications based on the CSSRI-EU have been demonstrated [26].

The European Quality of Life-Five Dimensions health status questionnaire (EQ-5D) is a short generic quality-of-life assessment [27] comprising EQ-5D five items: Mobility, self-care, usual activities, pain/discomfort, and anxiety/depression [28]. A five-digit number is derived that shows the person’s self-reported state of health. A visual analogue scale (EQ VAS), ranging from (0; worst imaginable health state) to (100; best imaginable health state) is also used to summarize the patient’s overall health state. The acceptance and validity of the EQ-5D for alcohol-dependent patients has been reported [29].

### Process evaluation measures used during treatment

A structured documentation form, which we developed, will be used to record all recommendations regarding further treatment that are given to the patient during withdrawal. For the patients in the IG, this includes (a) the LOC that is recommended based on the MATE, (b) therapists’ dissenting recommendations, if they occur, and reasons for the disagreement, (c) results from the feedback session, and (d) the final referral decision that was made at discharge. For patients of the CG, referral decisions are documented at discharge, using the same documentation form that is used for patients in the IG. In addition, research assistants complete a documentation form, which includes the number of patients who are eligible to participate in the study, the number of patients who agreed to participate, and for patients of the IG the number of referral decisions that are concordant with the recommendation that was derived from the MATE.

Patients are also asked to complete a questionnaire, which includes questions about alcohol use and psychosocial problems [30], the patients’ preferences regarding further treatment, and the Control Preference Scale (CPS) [31]. With the CPS, role preferences of patients regarding medical decision making, i.e. a passive, shared or active role, are assessed.

### Primary outcomes

The primary outcome measures will be alcohol consumption and health-care costs; they will be assessed six months after discharge from the current withdrawal treatment. Regarding alcohol consumption, per cent days of heavy drinking in the last 30 days (PDHD) was chosen as the primary outcome measure [32]. It is derived from the MATE-Outcomes*.* Health-care costs are estimated based on data on health-service utilization as assessed with the CSSRI-EU. The estimate includes a monetary valuation with unit costs.

Outcomes for the process evaluation include quantitative and qualitative data. In addition to the assessment instruments and documentation forms used during the trial, after the data have been collected, research assistants and heads of the participating treatment wards will be invited to attend a focus group to discuss potential benefits from and barriers for an implementation of the matching guidelines.

### Intervention

After the MATE interview with patients in the IG, the research assistant will review with the patient’s therapist or social worker, or both, the LOC recommendation based on the MATE results. In a subsequent feedback-session, the research assistant will explain the recommendation and will strive to reach a consensual decision with the patient regarding further treatment. In case a therapist has a diverging recommendation, this revised recommendation will be explained to the patient. At the end of the feedback session, the decision that the patient and research assistant have made will be documented, and the therapeutic staff will be informed about the decision.

Patients in the CG will not have an additional feedback session regarding their further treatment options and are treated as usual. These patients will receive global feedback regarding their assessment results, without a recommendation for a LOC, if they request it.

### Procedure

Immediately after admission to the withdrawal unit, patients will be invited to take part in the study. A research assistant will inform patients about the study procedure, and patients who wish to participate will be asked to sign an informed consent. Patients who have done so will be asked to complete a questionnaire prior to their first assessment. This assessment will be scheduled when a patient’s withdrawal symptoms have decreased to a minimal level as judged by the medical staff. During the assessment interview, a research assistant will administer the MATE, CSSRI-EU, and EQ-5D. Finally, the research assistant will be informed by the computer-assisted MATE, whether the patient has been randomly assigned to either the IG or the CG. For patients in the IG, the research assistant will schedule the feedback session.

At the end of the withdrawal treatment, all decisions and arrangements regarding subsequent treatment will be documented for patients in both the IG and the CG. Six months after discharge from the withdrawal treatment, patients are contacted for a telephone follow-up interview, which will include the MATE-Outcomes, CSSRI-EU, and EQ-5D. Patients who complete the entire procedure including the follow-up assessment will receive payment of 30 euros. The study procedure is diagrammed in Figure 2.

**Figure 2 Fig2:**
[figure not shown]
**Flowchart of patient progress through the qualified withdrawal unit and study procedure; MATE = Measurements in the Addictions for Triage and Evaluation; CSSRI = Client Sociodemographic and Service Receipt Inventory; EQ5D = EQ-5D Health questionnaire; IG = Intervention group; CG = Control group.**

### Randomization

Randomization occurs by means of computerized blocked randomization with varying block sizes that are stratified by trial site. Research assistants are blinded until the first assessment has been completed.

### Sample-size calculation

Due to the exploratory nature of the trial, the sample-size calculation was based on considerations regarding the process evaluation rather than the primary outcome measures. The concordance between MATE recommendations and actual referrals to the recommended LOC was considered to be an important mediator between the intervention and the outcome measures. Because classification into concordant (matched) and discordant (mismatched) decisions yields a cross-classification in addition to the LOC groups and study arms, it was important to ensure that in both study arms all of the cells include at least 10 analyzable cases at the six-month follow-up. Based on prior studies [11,19], we expected an imbalance between the four LOCs (approximate ratio: 1:3:5:1). Based on these assumptions, 100 analyzable cases would be needed in each arm at follow-up. Assuming a drop-out rate of 30 % between randomization and follow-up, 143 patients should initially be included in each study arm (or 286 patients in total). This sample size would ensure that subgroup analyses can be conducted, even if attrition rates are higher than expected or they differ among study arms or LOCs. Figure 3 shows the expected flow of patients.

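### The 100-per-arm figure gives 10 expected cases per level of care, so in LOC1 and LOC4 the matched and mismatched cells cannot both reach the required 10

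*Protocol article*

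**What the plan says.** All the relevant text is in the protocol article, Methods, Sample-size calculation. The size is based on the process evaluation and not on the primary outcomes. The reason given for a cell-count rule is that "classification into concordant (matched) and discordant (mismatched) decisions yields a cross-classification in addition to the LOC groups and study arms", and for that reason "it was important to ensure that in both study arms all of the cells include at least 10 analyzable cases at the six-month follow-up". The expected ratio of the four LOCs is given as approximately 1:3:5:1. The section then concludes: "Based on these assumptions, 100 analyzable cases would be needed in each arm at follow-up". With 30% drop-out between randomization and follow-up, "143 patients should initially be included in each study arm (or 286 patients in total"). It closes with an assurance: "This sample size would ensure that subgroup analyses can be conducted, even if attrition rates are higher than expected", or if attrition differs between arms or LOCs.

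The Statistical analyses section plans subgroup analyses of matched versus mismatched decisions in both arms and relates matching to the primary outcomes by multiple linear regression. The text gives no expected concordance rate, and the Discussion says that the frequency of therapist deviation cannot be estimated.

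**The concern.** The cell-count rule exists because of the matched/mismatched factor, yet that factor does not enter the calculation. The figure of 100 follows from the LOC ratio alone. If cells are counted as the section defines them, there are 4 × 2 = 8 per arm, and the two smallest LOCs supply too few patients for their two cells.

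This is the only justification given for N = 286. A reader who relies on it would expect at least 10 patients in every LOC-by-matching cell and a margin for extra attrition. The design provides neither, so matched/mismatched results within the small LOCs could be given more weight than their counts allow.

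**Working it through.** **Inputs** (Sample-size calculation): minimum of 10 per cell in each arm; LOC shares 10%, 30%, 50%, 10% from 1:3:5:1; 100 analyzable per arm; 30% drop-out; 143 randomized per arm. The concordance rate *c* (share matched) is not given. I assume 50% to 80%; 50% is the most favourable value.

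**1. Reproducing the plan's figure.** Using LOC × arm cells only: n per arm = 10 / smallest LOC share = 10 / 0.10 = 100. Drop-out: 100 / 0.70 = 142.9, rounded up to 143; 2 × 143 = 286. The stated figures are reproduced exactly, but only with the matched/mismatched factor left out.

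**2. Adding the factor.** Expected counts per LOC per arm are 100 × (0.1, 0.3, 0.5, 0.1) = 10/30/50/10. Splitting each into matched/mismatched as *c* : (1 − *c*):

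| *c* | LOC1 | LOC2 | LOC3 | LOC4 |
|---|---|---|---|---|
| 50% | 5/5 | 15/15 | 25/25 | 5/5 |
| 60% | 6/4 | 18/12 | 30/20 | 6/4 |
| 70% | 7/3 | 21/9 | 35/15 | 7/3 |
| 80% | 8/2 | 24/6 | 40/10 | 8/2 |

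In LOC1 and LOC4 the two cells sum to 10, so no value of *c* puts 10 in both. In LOC2, one cell falls below 10 when 30 × min(*c*, 1 − *c*) < 10, that is when *c* is above about 67% or below about 33%.

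**3. Size needed to meet the criterion in expectation.** n per arm = 10 / (0.10 × min(*c*, 1 − *c*)), divided by 0.70 and rounded up per arm:

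- *c* = 50%: 200 analyzable, 286 randomized per arm, 572 in total
- *c* = 60%: 250, 358, 716
- *c* = 70%: 334, 478, 956
- *c* = 80%: 500, 715, 1,430

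**4. Could rounding or chance rescue it?** LOC1 would need 20 cases per arm, twice its planned share. With zero drop-out it expects only 143 × 0.10 = 14.3, or 7.15 per cell at 50:50. If the LOC1 count is binomial(100, 0.10), the probability of 20 or more is 0.002.

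**5. Reserve for attrition.** 143 × 0.70 = 100.1, so the target is met with nothing to spare. At 35% attrition, 143 × 0.65 = 92.95 remain, and LOC1 and LOC4 each expect 9.3 per arm even before the matched/mismatched split. At 40%, 85.8 remain and each expects 8.6.

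**The case against.** **Cells may mean LOC × arm only.** That reading gives 100, but it empties the sentence that names the matched/mismatched cross-classification as the reason for the rule. Even then, 10 is an expected count and not an assured one. Taking the approximate ratio as exact, LOC1 reaches 10 in one arm with probability 0.55, LOC1 and LOC4 both do so with probability 0.28, and in both arms with probability 0.28² = 0.08.

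**Material not shown.** Figure 3, the expected patient flow, might give a matched/mismatched split. No split of 10 yields two cells of 10, so it cannot change the result.

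**No analysis within LOCs is actually planned.** This objection has force. A reader might infer that a LOC-specific matched/mismatched comparison is the main process analysis and that it fails. The documents do not support that: Statistical analyses states only effects of matched versus mismatched by multiple linear regression, and R1 to R3 name no LOC-by-matching comparison. A regression pooled across LOCs has about 100 patients per arm and does not depend on 10 per LOC1 cell.

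**The attrition sentence is not wholly false.** It says that subgroup analyses can be conducted, not that every cell keeps 10. With 93 or 86 patients per arm the pooled regression can still be run. What stands is that the assurance has no margin behind it for the 10-case target.

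**Conclusion.** The point holds. The section sets a criterion for LOC × matched/mismatched cells and gives a number that satisfies it only for LOC. At the expected counts, the matched and mismatched cells in LOC1 and LOC4 cannot both hold 10; this needs no assumption about concordance. One of the two could reach 10 only if the other were empty. The shortfall is at least a factor of two in analyzable patients (200 against 100 per arm) and grows as concordance moves away from 50%; sizes at particular rates rest on assumed concordance. There is no reserve against the 10-case target for attrition above 30%.

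A reader might also infer that the tests of H1 and H2 are compromised. They are not affected: the trial is exploratory and expressly not sized on the primary outcomes. The defect lies in the stated justification and in what can be expected of LOC-level process results, so it should be fixed but does not threaten the primary analyses.

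**What to change.** Keep N = 286 and change the text of Sample-size calculation:

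- State that 286 randomized patients give an expected 10/30/50/10 analyzable patients per LOC per arm at 30% drop-out, not 10 per matched/mismatched cell.
- Limit the closing assurance to the matched versus mismatched regression pooled across LOCs (about 100 per arm), and remove the claim of robustness to higher or uneven attrition as far as it concerns LOC-level cells.
- State that matched/mismatched results within LOC1 and LOC4 will be reported descriptively.

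Collapsing LOC1 with LOC2 and LOC3 with LOC4 (expected 40 and 60 per arm) is optional. If it is used, the text should say that it does not guarantee 10 per cell. With 100 analyzable per arm and the same concordance in every LOC, the probability that all four collapsed cells in one arm reach 10 is about 0.995 at 50% concordance, 0.97 at 60%, 0.77 at 70% and 0.20 at 80%. At 80% the mismatched LOC1+LOC2 cell expects only 40 × 0.2 = 8.

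The cost is rewording, with no extra patients. The downside is a less favourable stated justification and no separate inference for LOC1 and LOC4, which the expected counts could not support at the protocol's own 10-case standard.

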**Approximated patient flow of MATE-LOC.**

### Statistical analyses

All of the primary analyses will be conducted according to the intention-to-treat principle (ITT). There is a risk that not every patient in the IG will have a feedback session during his or her withdrawal treatment. This could result from time constraints for the therapists, unscheduled dropouts from treatment, or premature referrals for subsequent treatment. Therefore, additional per-protocol analyses will be conducted that include only those patients who actually participated in the intervention. In order to evaluate the robustness of the results, missing data will be addressed by using at least two procedures (e.g. complete case analyses, imputation by expectation-maximization, multiple imputation by chained equations), depending on the outcome and the patterns in the missing data. Differences between the two treatment arms regarding the primary outcomes will be analyzed using generalized linear models with gamma distribution and log-link function controlling for confounders (e.g. baseline costs and PDHD, age, gender, co-morbidity, EQ-5D scores). To account for correlated patient data caused by the multicenter structure, random-effect models will be applied.

Subgroup analyses will include effects of the classification as matched vs. mismatched decisions for patients in both the IG and the CG. That is, patients who received treatment according to MATE guidelines will be designated matched*,* and those who did not will be designated as mismatched. The effect of matching MATE recommendations with treatment received on the primary outcome measures will be analyzed using multiple linear regressions. Therapists’ documented reasons for deciding to deviate from MATE-LOC recommendations will also be analyzed in order to decide whether the decision algorithm should be modified. Additional exploratory analyses will be conducted to determine the relevance that patients’ demographic and clinical characteristics, their motivation for treatment, and their treatment preferences has for patient-treatment matching.

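### The sample size of 100 analysable per arm meets the 10-per-cell rule only before the matched/mismatched split; after it, at least one LOC1 and one LOC4 cell per arm is expected to hold 5 or fewer

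*Protocol article*

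**What the plan says.** The protocol article, Sample-size calculation, states that the trial was sized for the process evaluation and not for the primary outcomes. Concordance between the MATE recommendation and the actual referral is treated as an important mediator. The reason for the rule is that "classification into concordant (matched) and discordant (mismatched) decisions yields a cross-classification in addition to the LOC groups and study arms". The rule itself is that "it was important to ensure that in both study arms all of the cells include at least 10 analyzable cases at the six-month follow-up".

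The inputs that follow are the expected LOC distribution ("we expected an imbalance between the four LOCs (approximate ratio: 1:3:5:1") and the attrition allowance ("Assuming a drop-out rate of 30 % between randomization and follow-up"). The result is "Based on these assumptions, 100 analyzable cases would be needed in each arm at follow-up", raised to 143 randomised per arm and 286 in total. The section closes by saying that this size secures the subgroup analyses even if attrition is higher than expected or uneven across arms or LOCs.

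Under Statistical analyses, the article plans to use the split: "Subgroup analyses will include effects of the classification as matched vs. mismatched decisions for patients in both the IG and the CG". The effect of matching on the primary outcomes is to be analysed by multiple linear regression.

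**The concern.** The rule is motivated by a three-way table: 2 arms, 4 LOCs and 2 concordance states, which makes 8 cells per arm and 16 in all. The calculation uses only the LOC ratio. No concordance rate enters it, and none appears elsewhere in the article; the Discussion says that the frequency of therapist deviation from the recommendation cannot yet be estimated.

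The rule is the only justification given for 286 patients. If it is not met, the article credits the design with a property that it lacks, in the table that bears on the mediator it singles out. The shortfall would also grow with success: the more the intervention raises concordance above one half, the fewer mismatched patients remain in the intervention arm.

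**Working it through.** **Inputs (Sample-size calculation).** Minimum of 10 analysable cases per cell; LOC ratio 1:3:5:1, that is shares of 0.10, 0.30, 0.50 and 0.10; attrition 30%; equal arms. The concordance rate *m* is not given. It is assumed below, the same in every LOC and both arms, and shown over a range.

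**1. Reproducing the stated size.** 10 / 0.10 = 100 analysable per arm. 100 / 0.70 = 142.9, rounded up to 143 per arm, and 2 × 143 = 286. This matches exactly, but only with the matched/mismatched factor left out.

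**2. Expected counts per arm before the split.** 100 × (0.10, 0.30, 0.50, 0.10) = 10, 30, 50, 10.

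**3. Expected counts after the split.** Matched = LOC count × *m*; mismatched = LOC count × (1 − *m*).

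| Assumed *m* | LOC1 and LOC4, each | LOC2 | LOC3 | Cells below 10, of 8 per arm |
|---|---|---|---|---|
| 30% | 3 / 7 | 9 / 21 | 15 / 35 | 5 |
| 40% | 4 / 6 | 12 / 18 | 20 / 30 | 4 |
| 50% | 5 / 5 | 15 / 15 | 25 / 25 | 4 |
| 60% | 6 / 4 | 18 / 12 | 30 / 20 | 4 |
| 70% | 7 / 3 | 21 / 9 | 35 / 15 | 5 |
| 80% | 8 / 2 | 24 / 6 | 40 / 10 | 5 |

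Each LOC1 and LOC4 pair sums to 10. The smaller cell is therefore 5 or fewer at any *m*, and neither cell reaches 10 unless the other is empty. This needs no assumption about concordance; only the exact split does.

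**4. Size that would meet the rule in expectation.** Analysable per arm = 10 / (0.10 × min(*m*, 1 − *m*)); divide by 0.70 and round up for randomised per arm, then double.

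- *m* = 50%: 10 / 0.05 = 200; 200 / 0.70 gives 286 per arm, 572 in total.
- *m* = 40% or 60%: 10 / 0.04 = 250; 250 / 0.70 gives 358 per arm, 716 in total.
- *m* = 30% or 70%: 10 / 0.03 = 333.3, so 334; 334 / 0.70 gives 478 per arm, 956 in total.

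The first line is the floor: two cells of 10 need 20 patients, and 20 / 0.10 = 200.

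**5. The narrower reading, cells as LOC by arm only.** At 30% attrition, 143 × 0.70 = 100.1 per arm, so the small LOCs expect 10.0. At 35%, 143 × 0.65 = 92.95, and they expect 9.3. At 40%, 143 × 0.60 = 85.8, and they expect 8.6. With exactly 100 analysable per arm and the stated shares, the probability that a given small LOC reaches 10 is P(Bin(100, 0.1) ≥ 10) = 0.55. By multinomial simulation, LOC1 and LOC4 both reach 10 in one arm with probability 0.28, and in both arms with probability 0.28² ≈ 0.08.

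**The case against.** **The cells may have been meant as LOC by arm.** The rule is followed only by the LOC ratio, and 100, 143 and 286 then reproduce exactly, so the fault could be loose wording. This reading sets aside the reason that the sentence itself gives for the rule. It also leaves an expected count of exactly 10 with no reserve, so neither the guarantee nor the robustness to higher attrition would hold. The small probabilities in step 5 are a secondary point: planning on expected counts is common, and the article calls its ratio approximate. They count only against the promise of a guaranteed minimum.

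**The planned analysis may not need 10 per cell.** This stands. Statistical analyses names multiple linear regression and specifies no separate matched/mismatched contrast within LOC1 or LOC4. A reader might infer that the trial plans five-against-five comparisons in those groups and presents them as adequately sized. The documents do not say so, and they give no standard deviation from which to work out the precision of such a comparison.

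**The trial is exploratory.** This also stands and limits the weight of the point. The article says that the primary outcomes did not set the size, and the Discussion says that a larger trial will be needed. It does not answer the arithmetic, because the rule is stated and the stated calculation does not meet it.

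Figure 3, the expected patient flow, is not available in the text reviewed. No split shown there could make 10 patients fill two cells of 10.

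**Conclusion.** The point holds. Read as its own reasoning requires, the rule is not met in LOC1 or LOC4 in either arm, even with attrition exactly as assumed. At least one cell of each pair is expected to hold 5 or fewer, and about 2 to 5 for concordance between 20% and 80%. Meeting the rule in expectation would take at least twice the stated size. The shortfall rests only on the article's own LOC ratio, attrition and target; the figures by concordance rest on an assumed common rate.

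Two stronger readings are not supported. One is that every LOC1 and LOC4 cell will hold 5 or fewer: that is so only at 50% concordance, and otherwise the larger cell of the pair exceeds 5 (7 against 3 at 70%). The other is that the primary comparisons are compromised: no primary hypothesis test depends on this rule. It should be fixed as a correction to the stated basis of the sample size; it does not require a larger trial.

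**What to change.** In Sample-size calculation:

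- State that 100 analysable patients per arm give an expected 10, 30, 50 and 10 per LOC per arm before the matched/mismatched split, and that the smaller LOC1 and LOC4 cells after the split are expected to hold about 2 to 5. Name the concordance range assumed.
- Withdraw the claim that all cells hold at least 10, the wording that this is ensured, and the claim that the size is robust to attrition above 30%.

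In Statistical analyses:

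- State that the matched/mismatched effect will be estimated across LOCs in the planned regression with LOC as a covariate, and that no separate matched/mismatched estimate is claimed within LOC1 or LOC4. Whether to pool any LOCs is the sponsor's choice.

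The cost is wording only, with no added patients. The downside is a less favourable stated property and no matching estimate specific to LOC1 or LOC4.
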